## Abstract

**Background:**

Despite the availability of evidence-based treatments for depression, a large proportion of patients remains untreated or adequate treatment is initiated with delay. This situation is particularly critical in primary care, where not only most individuals first seek help for their mental health problems, but also depressive disorders – particularly mild to moderate levels of severity – are highly prevalent given the high comorbidity of chronic somatic conditions and depression. Improving the access for evidence-based treatment, especially in primary care, is hence a priority challenge in the mental health care agenda. Telephone usage is widespread and has the potential of overcoming many barriers that individuals suffering from mental health problems are facing: Its implementation for treatment delivery presents an option for optimisation of treatment pathways and outcomes.

**Methods/design:**

This paper details the study protocol for a randomised controlled trial (RCT) evaluating the effectiveness of a telephone-administered short-term cognitive-behavioural therapy (T-CBT) for depression as compared to treatment as usual (TAU) in the Swiss primary care setting. The study aims at randomising a total of 216 mildly to moderately depressed patients, which are either identified by their General Practitioners (GPs) or who self-refer to the study programme in consultation with their GP. The trial will examine whether telephone-delivered, manualised treatment leads to clinically significant reduction in depression at follow-up. It will further investigate the cost-effectiveness and acceptability of the intervention in the primary care setting.

**Discussion:**

Conducting a low-intensity treatment on the telephone allows for greater flexibility for both patient and therapist, can grant more anonymity and can thus lead to less hesitation in the patient about whether to attempt treatment or not. In order to benefit from this approach, large-scale studies need to prove superior effectiveness and cost-effectiveness of telephone-delivered therapy over routine care for patients with mild to moderate depression.

**Trial registration:**

ClinicalTrials.gov NCT02667366. Registered on 3 December 2015.

## Background

Depressive disorders are a common mental health condition with a high prevalence and burden of disease. With a 12-month prevalence of approximately 8% it is one of the most widespread mental disorders [1] and causes a high degree of personal suffering and impairment. It is also associated with high societal costs, thus presenting a substantial challenge to the health care system, not least in view of the considerable direct and indirect costs implied [2]. In Switzerland, for example, the total cost caused by depression on a national level amounts to more than 8 billion Swiss Francs per year [3]. Estimations predict a further increase in depression-related disease burden in the next 20 years; depression will represent the second most important factor for impairment and premature mortality after cardiovascular diseases in highly economically developed countries [4].

**Mild to moderate depression** presents a particular challenge to the health care system for various reasons. Firstly, there is a high prevalence of these levels of depression among the general population. In a national representative data sample in the US, an overall prevalence of 20% of any depressive symptoms was assessed, the majority of which were mild to moderate depressive symptoms [5]. Secondly, the nature of mild to moderate depressive episodes involves the risk of exacerbating symptoms and developing chronic or more severe forms of the depressive disorder if they remain untreated, are inadequately treated or if treatment is initiated with delay [6]. In order to treat depressive disorders efficiently and in order to avoid deterioration of the individuals’ condition and increase of the societal burden, the provision of timely and adequate treatment is of great importance. Therefore, inappropriate health care for patients suffering from depression poses a third challenge for the health care system: according to international trials, treatment adequacy is particularly low in mild to moderate degrees of depression [7]. In primary care, almost two thirds of patients suffering from mild depression and one third of patients suffering from moderate depression receive exclusively antidepressant medication [6], even though international guidelines recommend psychotherapy and low-intensity treatment – with a particular focus on cognitive-behavioural therapy (CBT) – as first-line treatment [8, 9]. These clinical guidelines further explicitly advise against the application of antidepressant medication in mild degrees of severity except for special situations, due to the unfavourable risk-benefit ratio with regard to undesirable side effects. Treatments that are not compliant to clinical guidelines consequently present a serious problem for patients suffering from less severe depressive disorders.

However, initiating adequate psychological treatment is impeded by various barriers to access care on an individual level (fear of stigma, lack of time, comorbid somatic conditions, cultural factors), on the provider level (inadequate diagnostics and knowledge about mental disorders in primary care, lack of time) and on the systemic level (waiting lists, insufficient interconnectedness between health care professionals, insufficient treatment capacity) [10].This inadequate supply situation particularly affects primary care, given the high prevalence rates of depression there (ranging between 5 and 30%) [11] with general practitioners (GP) being in charge of detecting patients, motivating them for treatment and initiating it. The latter comprises either treatment in primary care or the referral to specialized care, which is rather seldom (e.g. in Switzerland only approx. 13%, (e.g. [12])).

Given these challenging tasks in (primary) care, low-threshold and intensity-appropriate (so-called `low intensity´) formats of psychological treatments, such as telephone-administered psychotherapy, may contribute to a better access to evidence-based treatment.

### Telephone-administered psychotherapy

One increasingly promising approach to overcoming the aforementioned barriers is the application of treatments with the help of remote communication. Telephone and particularly mobile phone is an omnipresent and well-accepted means of communication [13], which has become a reliable tool for managing and delivering care in many areas of the health care system and for a variety of somatic conditions [14, 15]. Telephone-based interventions focusing on mental health have further been proven beneficial and effective in providing CBT for a variety of mental disorders and symptoms, including anxiety disorders in older patients [16], insomnia, health-related quality of life and disability [17] and a variety of conditions where mental health problems co-occurred with chronic somatic disorders. Telephone-delivered psychotherapy – with a special emphasis on CBT (T-CBT) – also shows promising results for the treatment of depression in international meta-analyses [18]. Trials that have thus far investigated this approach for depression in primary care settings have shown lower attrition rates and equivalent improvement in symptom severity at posttreatment compared to face-to-face treatment [19, 20]. Thus, T-CBT could lead to expanded, more flexible, and accessible psychotherapeutic services with the additional option of lowering costs.

However, the majority of trials aim at the reduction of depressive symptoms in patients suffering from chronic and distressing somatic conditions, such as HIV/AIDS, multiple sclerosis and cancer [21–23]. Other studies do not examine T-CBT as a stand-alone treatment for depression; for example, some studies focus on T-CBT in depression care management [24, 25] or as adjunct support in order to ensure adherence to pharmacological treatment. It is also insufficiently clarified whether T-CBT has long-lasting effects on the patients’ mental health and if long-lasting effects would pertain to a less severely depressed patient sample [19].

Despite promising results for T-CBT for depression in primary and specialist care [18, 26], it is necessary to investigate an intensity-appropriate therapy delivered via telephone as a stand-alone intervention as well as to examine effects that go beyond the post-treatment improvement for patients with mild to moderate depression. Lastly, large-scale effectiveness studies with more specific patient samples are required to add to a solid evidence-base and need to be adopted to the specific characteristics of various health care systems. The proposed trial enables us to investigate whether T-CBT as a stand-alone treatment element can improve the acute treatment of mild to moderate depression, which will be undertaken in the Swiss health care system.

### Objectives

Our study aims at evaluating the effectiveness of a telephone-delivered CBT as an add-on treatment to routine care in primary care patients with mild to moderate depression under clinically representative conditions. Secondary objectives include the evaluation of T-CBT’s cost-effectiveness compared to treatment as usual (TAU). Further objectives are the examination of process variables. Particularly, patients’ and therapists’ acceptance and satisfaction with the telephone-intervention as well as process quality of the treatment and therapeutic alliance will be investigated.

### Hypotheses

Primary hypothesis is that the addition of T-CBT to routine care is superior to routine care alone (treatment as usual, TAU) in reducing depression symptom severity measured with the Patient Health Questionnaire (PHQ-9) at 12-month follow-up. Main secondary hypotheses are that T-CBT is more effective at reducing symptom severity at end of treatment (t1) and that T-CBT is cost-effective compared to TAU.

### Ethical approval

Approval for the study has been obtained from the responsible local Ethics Committee of the Canton of Zurich (Ref. Nr. 2015–0417). The study will be conducted according to the principles of the Declaration of Helsinki and in line with the Guidelines for Good Clinical Practice (GCP).

## Methods: Participants, interventions, and outcomes

### Study design

The proposed study is a prospective randomised controlled effectiveness trial of short-term T-CBT compared to treatment as usual in primary care patients with mild to moderate depression. Both study arms will receive treatment as usual (TAU). A total of 216 individuals who fulfil inclusion criteria are intended to be randomised in either active treatment or control condition with a 1:1 allocation. Outcomes will be assessed at baseline (t0), at the end of treatment (t1, i.e. 4 months after baseline in CG) and 12 months (t2) after baseline. Table 1 presents a structured summary of the trial by providing items from the WHO Trial Registration Data set.

**Table 1 Tab1:** WHO Trial Registration Data Set

Data category	Information
Primary registry and trial identifying number	ClinicalTrials.gov NCT02667366
Date of registration in primary register	3 December 2015
Sources of monetary or material support	Gottfried and Julia Bangerter-Rhyner-Foundation (Bangerter-Stiftung) and Swiss Academy of Medical Sciences (Schweizerische Akademie der Medizinischen Wissenschaften, SAMW)
Primary sponsor(s)	[name], University of Zurich
Contact for public queries	M.Sc. [name] Department of Clinical Psychology and Psychotherapy Research [name] Switzerland [contact]
Contact for scientific queries	[name]. [name] Department of Clinical Psychology and Psychotherapy Research [name] Switzerland [contact]
Public title	Telephone-Intervention/Information for Depression (TIDe)
Scientific title	Effectiveness and cost-effectiveness of a telephone-based cognitive-behavioural therapy in primary care for mild to moderate depression
Countries of recruitment	Switzerland
Health condition(s) or problem(s) studied	Mild to moderate depression
Intervention(s)	Telephone-delivered short-term cognitive-behavioural therapy
Key inclusion and exclusion criteria	Inclusion criteria: Age ≥ 18 years, mild to moderate depression according to ICD-10, PHQ-9 > 5 and ≤15, able to fill in questionnaires, German language Exclusion criteria: suicidality or suicidal tendency, currently or in last 3 months in psychotherapeutic treatment, chronic depression or dysthymia, severe depression, psychopharmacological medication that is not stable for 3 months prior to enrolment.
Study type	Randomised-controlled superiority trial
Date of first enrolment	January 2016
Target sample size	216
Recruitment status	Recruiting
Primary outcome(s)	Symptom severity at t2 (PHQ-9)
Key secondary outcomes	Symptom severity at t1 (PHQ-9), Response defined as 50% reduction from t0 to t1,remission defined as <5 points in the PHQ-9 at t2 and t1, relapse defined as ≥5 points in the PHQ at t2 following remission at t1, cost-effectiveness

### Participants

The trial aims at randomising a total of 216 patients with mild to moderate depression, who are either recruited by a participating GP in Zurich or who take notice of the study advertisement in the media (esp. regional newspapers) and thus self-initiate study participation in consultation with their GP.

#### Inclusion criteria

Eligible study participants need to meet the following inclusion criteria: a) age of at least 18 years, b) PHQ-9 score of >5 and ≤15, c) a diagnosis of mild or moderate depression according to ICD-10, more specifically a single episode major depressive disorder or recurrent depressive disorder with a mild or moderate degree of severity (i.e., F32.0, F32.1, F33.0, F33.1) and d) given informed consent.

#### Exclusion criteria

The following criteria lead to exclusion from the study: a) chronic depression i.e. symptoms of at least 2 years duration, b) suicidality, suicidal tendency or suicidal ideation, c) insufficient knowledge of the German language, d) taking part in psychotherapeutic / psychological treatment currently or in the last 3 months, e) a physical or mental condition that does not allow the completion of questionnaires. Psychopharmacological treatment is only an exclusion criteria, if medication is not stable for at least 3 months prior to study inclusion.

### Study interventions

#### T-CBT (intervention group)

The intervention group (IG) will receive T-CBT in addition to TAU, which is a short-term telephone-delivered psychotherapy. The therapy programme is a manualised cognitive-behavioural therapy (CBT) consisting of one initial face-to-face appointment and 8–10 subsequent telephone sessions (+ 2 optional booster sessions) with the study therapist. Telephone contacts will take place on a weekly and – after the first four sessions – on a bi-weekly basis and will last 3–4 months in total. Each telephone contact should last between 30 and 40 min and will be audio recorded for the sake of assessing treatment integrity and evaluating treatment process variables.

The therapy programme is a translated and culturally adapted version of the programme *Creating a balance* developed in the US [24, 27]. The German version (“Ins Gleichgewicht finden”) has been evaluated as part of a stepped care trial [28], i.e. was part of a complex intervention of stepped care which was evaluated as a whole. For the proposed study, the manual has been adapted slightly according to special characteristics and cultural features of the Swiss population (especially adaption of the case studies, e.g. using typical Swiss expressions and names).

The manualised programme comprises the central components of CBT for depression: the first part of the programme focuses on behavioural activation and the subsequent chapters centre upon strategies of cognitive restructuring. Further essential treatment elements are psycho-education and relapse prevention. After a maximum of 10 sessions there is the option of adding up to two booster sessions for enhancing long-term maintenance of treatment effects. Patients receive a workbook which they work with independently between sessions and then discuss materials with the telephone therapist. Moreover, since regular symptom monitoring (PHQ-9) is part of the telephone treatment, patients learn to monitor themselves concerning their depressive state. Despite the strong structure and guidance provided by the therapist, the programme has a strong self-help character and thus requires patients to delve into the contents and acquire skills themselves with support of the therapist.

T-CBT will be conducted by three study therapists in training, who are clinical psychologists and are in CBT training with a minimum of 2 years of experience in the treatment of patients predominantly suffering from affective disorders. The study therapists receive training in T-CBT and supervision will be provided every month by a senior study team member (BW).

Adverse events will be regularly and systematically monitored by the telephone therapist. Emergency plans will be prearranged in case of acute suicidality, e.g. calling the emergency services. In case of an emotional decompensation there will be the possibility to meet in a face-to-face session or to choose a more intensive treatment (e.g. inpatient treatment).

#### Text messages (control group)

Patients in the control group (CG) will receive TAU and a minimal intervention additionally: This minimal intervention entails a total of 10 text messages which contain factual information on depression. The text messages will be sent to the patient on a weekly and later bi-weekly basis, i.e. in the same frequency as telephone-sessions in the IG. The receiver cannot and is not required to reply to the messages. The messages contain short neutral information on different aspects of depressive disorders, for example on prevalence, clinical picture, course and the social implications of the depressive disorder (e.g. “Depression is very common. More than every fifth person experiences depression once in their life”). The text messages should be of interest for the patients in the control condition without having a therapeutic effect. The contents of the text messages differ from a psychoeducational intervention in the sense that they a) do not follow a systematic and structural knowledge transfer and b) do not convey strategies that enable a health-promoting lifestyle. The minimal intervention is amended to TAU to control for effects resulting from purely contacting patients and reminding them. It can be assumed that they might have a minimal effect on patients on the short term, but not a lasting (therapeutic) one.

### Outcomes and measures

#### Outcome assessment

Outcomes will be assessed via self-report paper-pencil questionnaires at baseline, post-intervention and follow-up, which will be sent to the patient via mail. The primary outcome of effectiveness refers to a change in symptom severity from t0 (baseline) to t2 (12 months after baseline), measured by the German version of the PHQ-9.

Secondary outcome parameters will include the change in depressive symptoms from t0 to t1, response defined as a 50% reduction in the PHQ-9 value from t0 to t1, remission defined as <5 points in the PHQ-9 at t2 and t1, and relapse defined as ≥5 points in the PHQ-9 at t2 following remission at t1. Further secondary outcome is change in health-related quality of life (HrQoL) assessed by the SF-12. Furthermore, the incremental cost-effectiveness of T-CBT compared to TAU will be analysed based on (direct and indirect) costs and quality-adjusted life years (QALYs) observed within the 12-month follow-up period.

In addition to outcome measures, there will be an assessment of structural and process variables. For the IG, these will entail amount and duration of telephone contacts as well as contents of the sessions. Additional assessments take place at the beginning of each telephone session in order to monitor symptom severity and measure therapist ratings regarding the therapeutic alliance between patient and therapist. Therapists’ and patients’ acceptance of and satisfaction with T-CBT will be assessed with a self-constructed questionnaire based on instruments from the study team’s prior research.

#### Outcome measurements

**Patient Health Questionnaire (PHQ-D):** is the German version of a patient rating instrument covering the severity and frequency of symptoms of depression (9 items), generalised anxiety syndrome (7 items), somatoform syndrome (13 items) and panic syndrome (11 items). The instrument demonstrates high levels of validity in the diagnosis and evaluation of symptom severity of major depressive disorder in primary care patients [29]. The PHQ-D is a well-accepted, reliable instrument and shows diagnostic validity [30]. The depression subscale (PHQ-9) covers severity/frequency of the primary and secondary symptoms of major depressive disorder [29] and has proven reliability and validity for the use in primary care [31].

**Short Form − 12 (SF-12):** is the short version of the Short Form 36 Health Survey and assesses overall health-related quality of life. The 12 items constitute the two subscales physical and mental health. It is an internationally well-established instrument with proven psychometric properties [32].

**General Self-Esteem Scale (GSES):** is a revised version of the Rosenberg Self-Esteem-Scale and captures global, unidimensional self-esteem. Ten statements regarding beliefs about personal ability, value and attitudes toward oneself are rated on a 4-point Likert scale. Reliability and validity show satisfactory values [33].

**General self-efficacy scale (GSE):** is a one-dimensional self-rating scale measuring the global optimistic beliefs about one’s self [34]. On a four-point Likert scale, subjects indicate their level of agreement with ten statements about the self-related expectation of coping with a difficult situation.

**Depression-related self-management behaviour:** this five-item scale was created to examine the respondents’ perceived ability to cope with depressive symptoms and complaints [35] and to assess to which extent patients integrate pleasant activities in their daily lives.

**Client Sociodemographic and Service Receipt Inventory (CSSRI):** will be employed to measure health care utilisation and productivity loss [36]. A slightly adapted version of the instrument for the Swiss health care system will assess the type and frequency of all health services the respondent used as well as absence from work during the last 6 months.

**EQ-5D-5 L:** Health-related quality of life for the economic analysis will be measured using the EQ-5D-5L, an internationally established instrument to derive utilities (EQ-5D index) for cost-effectiveness analyses [37] (www.euroqol.org).

**Psychotherapy Motivation Questionnaire (FPTM-23):** is the short version of the Questionnaire on Psychotherapy Motivation [38], a measure used to assess the motivation for undertaking a psychotherapy. Three out of six sub-scales – psychological stress, hope and denial of need for help – are used in this study. These sub-scales also indicate sufficient and good internal consistency [38].

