### Recruitment and study procedure

The recruitment process entails two main strategies. In the first instance, study patients will be recruited by 15 participating GPs in the area of Zurich, Switzerland. All patients visiting their GP who are at risk for depression, especially those who present diffuse somatic or chronic somatic symptoms [8] will be screened for depressive symptoms. The GP who has been trained by the study team has two alternative ways of proceeding with study inclusion: a) the GP carries out diagnostics and conducts study enrolment by checking eligibility criteria, obtaining the consent form and handing out the baseline questionnaire; b) the GP alternatively refers the patient directly to the study team: If the patient consents to being contacted, a member of the study team will call the patient and will carry out ICD-10 diagnosis and study enrolment over the telephone. Baseline questionnaire and consent form will be sent via mail.

The second strategy of participant recruitment will be patient-initiated enrolment. Newspaper articles describing the study and the option of participating will be published in regional newspapers and on the homepage of clinical units in Zurich. Patients initiating contact with the study team via telephone will be screened by the study team, who will carry out ICD-10 diagnosis and study enrolment over the telephone. Additionally, patients need to consult their GP and inform them about study participation. Signed consent forms and baseline questionnaire will be sent via mail (see section “consent and confidentiality”). After the study team receives the signed informed consent and baseline questionnaire, patients are enrolled and subsequently randomised.

Patients allocated to the IC will be called by a member of the study team to arrange an appointment between patient and study therapist ideally within 1 week after randomisation. If a patient is assigned to the CG, the first text message will be sent within a week after randomisation. Four months and 12 months after t0, all patients will receive mail from the study team containing the t1-questionnaire and a stamped envelope to return the completed questionnaire. If a patient fails to return the questionnaire, at first one written reminder for filling out the questionnaire will be sent, and, if still unsuccessful, the patient will be reminded by a phone call. For each completed follow-up questionnaire, patients will receive a CHF 25.-shopping voucher.

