### Statistical analysis

Data will be analysed according to the CONSORT statement [39]. The primary analysis will refer to the intention-to-treat (ITT) sample that includes all randomised eligible patients. Multiple imputation of missing data will be performed if data required for the primary analysis are missing. For the primary outcome ‘PHQ-9 change in depressive symptoms from t0 to t2’ an analysis of covariance (ANCOVA) with baseline PHQ-9 as covariate and group as fixed effect will be calculated in order to estimate and test the difference between the IG and the CG. The secondary outcomes will be examined in an exploratory manner with appropriate procedures. Sensitivity analyses will be performed by application of an alternative imputation method (last observation carried forward, LOCF), inclusion of further covariates and restriction to complete cases or to the per protocol population (PP sample) consisting of patients without major violations of the study protocol. The decision whether a protocol violation is judged as major will be blindly met by the study team. Interim analyses are not planned. The significance level will be set at 5% (two-sided). Statistical analyses will be carried out with SPSS, Version 23 (IBM Corp., Armonk, NY, USA).

In order to determine the cost-effectiveness of T-CBT, health care utilisation and productivity loss measured with an adapted version of the CSSRI will be monetarily valued by Swiss unit costs to calculate direct and indirect costs. Quality-adjusted life years (QALYs) will be calculated based on the EQ-5D index [40], and the incremental cost-effectiveness ratio (ICER) will be computed. To adjust for baseline differences and to evaluate the uncertainty of the estimates, net-benefit regressions will be conducted and cost-effectiveness acceptability curves will be derived therefrom.

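### A fixed 6-month cost recall at visits set at 0, 4 and 12 months leaves months 4 to 6 unobserved, so the 12-month cost is not fully observed as stated

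*Protocol article*

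**What the plan says.** All statements are in the protocol article.

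- **Recall period.** Under Outcome measurements, the adapted CSSRI is to "assess the type and frequency of all health services the respondent used as well as absence from work during the last 6 months". One period is given and it does not change by visit.
- **Visit times.** Study design places assessments at baseline, "at the end of treatment (t1, i.e. 4 months after baseline in CG) and 12 months (t2) after baseline". Recruitment and study procedure agrees: "Four months and 12 months after t0, all patients will receive mail from the study team". Outcome assessment names the same three occasions and no others: "Outcomes will be assessed via self-report paper-pencil questionnaires at baseline, post-intervention and follow-up".
- **Costing horizon.** Under Outcome assessment, incremental cost-effectiveness is "based on (direct and indirect) costs and quality-adjusted life years (QALYs) observed within the 12-month follow-up period".
- **Source of the costs.** Under Statistical analysis, service use and lost productivity "measured with an adapted version of the CSSRI will be monetarily valued by Swiss unit costs to calculate direct and indirect costs". No other source is named for these two components.
- **Standing of the result.** The Hypotheses section makes cost-effectiveness one of the main secondary hypotheses. Statistical analysis says that secondary outcomes are examined in an exploratory way.

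**The concern.** A recall questionnaire yields a complete cost total only if its windows join end to end across the follow-up period. A 6-month window would do that with visits at months 6 and 12. This trial's visits after baseline are at months 4 and 12.

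The mismatch is easy to miss. Two 6-month reports add up to 12 months, so a simple sum of t1 and t2 looks like a year of cost. It is not the year that follows randomisation, over which the QALYs are measured. The gap also comes straight after the 3 to 4 months of treatment, when service use and work absence could differ between arms. Whether they do differ cannot be told from the article.

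The quantities at stake are the incremental cost, the ICER, the net-benefit regression and the acceptability curves. What a form never asked about can later be modelled, but not observed.

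**Working it through.** **Inputs.** Recall length 6 months (Outcome measurements). Visits at months 0, 4 and 12 (Study design; Recruitment and study procedure). Costing horizon months 0 to 12 (Outcome assessment).

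**Coverage.** A form completed at month v with 6-month recall covers months v - 6 to v.

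| Form | Window (months) | Part inside follow-up | Part before baseline |
|---|---|---|---|
| t0 | -6 to 0 | none | 6 months |
| t1 | 4 - 6 = -2 to 4 | 0 to 4 (4 months) | 2 months |
| t2 | 12 - 6 = 6 to 12 | 6 to 12 (6 months) | none |

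- Follow-up observed: 4 + 6 = 10 of 12 months. The stated 12 months of observed cost are not reproduced.
- Gap: months 4 to 6, that is 2/12 = 16.7%.
- Share of the t1 window before baseline: 2/6 = one third. The t0 form covers the same two months.
- Nominal recall in t1 + t2: 6 + 6 = 12 months, of which 10 belong to follow-up.

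**Sensitivity to the timing of t1.** With t2 at month 12, the gap and the pre-baseline part are each 6 - v months, where v is the month of t1. This gives 3 months at v = 3 (treatment ending early in the intervention group, if t1 were tied to it), 2 at v = 4, 1 at v = 5 and 0 only at v = 6.

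**Effect on the difference between arms.** Let D1, Dg and D2 be the expected differences in cost in months 0 to 4, 4 to 6 and 6 to 12. The target is D1 + Dg + D2. Months -2 to 0 precede randomisation, so their expected difference is 0.

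- Whole t1 form: expected difference 0 + D1 = D1. Arm means rise and variance is added, but the contrast is not shrunk.
- Sum of t1 and t2: D1 + D2. The shortfall is exactly Dg, whose sign and size the article does not give.
- t1 multiplied by 4/6: expected difference 0.67 D1, a loss of one third. This repair would create a bias that the whole form does not have.
- t1 minus 2/6 of the t0 cost: the t0 cost has expected difference 0, so the result is D1 - 0 = D1.

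**Coverage with matched windows.** Four months at t1 covers 0 to 4 and eight months at t2 covers 4 to 12. Together that is 4 + 8 = 12 of 12 months, with no gap and no time before baseline.

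**The case against.** The strongest reply is that the article gives no rule for combining the three reports. Pro-rating and extrapolation belong in an analysis plan, which is not shown. This stands in part. A reader might infer that months 4 to 6 will be left out of the costing altogether, or that two pre-baseline months will certainly be counted as follow-up. The article supports neither statement. What it does fix is the recall length, the visit times and the claim that the costs are observed over 12 months. An analysis plan can fill the gap with an estimate, but those two months would then not be observed.

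A reader might also infer that the pre-baseline months dilute the cost contrast. They do not, as shown above. The planned net-benefit regression adjusts for baseline differences, so if the CSSRI is collected at t0, chance imbalance in those months can be handled. That adjustment does not recover months 4 to 6.

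A third tempting reading is that the CSSRI is used only at t0 and t2, which would leave half the year uncovered. Nothing in the article suggests this. The participant flowchart might list instruments by visit, but it is not shown here, and the text places outcome assessment at all three occasions.

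Finally, 17% is a share of calendar time, not of incremental cost, and no effect on the ICER has been shown. That is correct, and it limits the severity.

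**Conclusion.** The point holds as a mismatch between the recall period, the visit schedule and the stated costing horizon. On the article's own figures, 2 of 12 follow-up months (17%) are observed by no form, and one third of the t1 window precedes randomisation. The first is the real loss. The second costs precision and inflates the arm means, but leaves the expected difference in total cost intact.

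This rests on three assumptions: the CSSRI is given at both t1 and t2, the forms are completed close to months 4 and 12, and the 6-month wording applies at each visit. If the forms in use already carry other windows, the description under Outcome measurements needs correcting instead.

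The direction and size of any bias in the ICER cannot be determined. The primary PHQ-9 analysis is unaffected. Because a main secondary hypothesis depends on the cost total, this should be fixed.

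**What to change.** **Forms still to be sent.** Set the CSSRI window to the interval since the previous assessment: the last 4 months at t1 and the last 8 months at t2. Keep the t0 form for baseline adjustment. State these windows under Outcome measurements so that they agree with the schedule and the 12-month horizon.

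**Forms already returned with the 6-month wording.**

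1. Do not multiply t1 by 4/6.
2. Subtract a pre-baseline share estimated from t0 (for example 2/6 of the t0 cost, assuming even use over that window). Alternatively, keep the t1 total and adjust for t0 cost in the regression.
3. Impute months 4 to 6 from the t1 and t2 monthly rates. The t1 rate should be the reduced t1 cost divided by 4, because dividing the whole form by 6 brings the attenuation back. With a simple average of the two rates, the imputed cost is 2 x ½ x (reduced t1/4 + t2/6).
4. Report months 4 to 6 as modelled, and vary the imputation in a sensitivity analysis.

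**Cost.** New recall wording on two forms and one written costing rule. An 8-month recall carries more recall error than a 6-month one. Table 1 lists the trial as recruiting, so a change now would mix recall windows within the cost variable; the version each patient received should be recorded. The subtraction in step 2 adds noise and can give negative values for single patients.
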